**Fig. 1 Fig1:**
[figure not shown]
Community-based pulmonary rehabilitation – exercise training component. 6MWT – 6-min walk test; Wpeak - work peak; HRmax – maximum heart rate; 1-RM – 1 repetition maximum; 10-RM – 10 repetition maximum; N/A – not applicable. Consent from participants was obtained to publish the data

Each education and psychosocial session will last approximately 90 min. Six sessions will be conducted by a multidisciplinary team. Based on the literature and previous experience, it is anticipated that some themes will need to be addressed [42, 81–84] however, the component will be tailored to patients and caregivers’ needs. A detailed description of these sessions can be found in Fig. 2.

**Fig. 2 Fig2:**
[figure not shown]
Community-based pulmonary rehabilitation – education and psychosocial component

Patients will also receive recommendations for home training to complete on the additional days: i) aerobic, resistance and balance exercises and general health counselling to perform ⩾30 min of moderate physical activity ⩾5 days per week [85]. A leaflet with some exercise options and physical activity guidance will be provided (Fig. 3). Moreover, they will sign a physical activity contract, which consists of encouraging self-efficacy and establishing individualised goal setting [86]. For this purpose, the final goal of steps average count will be negotiated with the patients, accordingly to their baseline, i.e., those with > 9000 steps/day - maintain or increase steps/day; those with ≥6000 and < 9000 steps/day - reach 9000 steps/day and in those with < 6000 steps - increase 3000 steps/day by the end of the programme [87]. Furthermore, the physiotherapist will provide weekly-feedback to encourage patients to increase 562 steps every week [88]. Participants will receive a pedometer and a physical activity diary, to register their daily steps.

**Fig. 3 Fig3:**
[figure not shown]
Exercise options and physical activity recommendations for patients to perform at home

The CG will continue to receive the standard care from the primary healthcare team.

### Sample size

A sample size estimation with 80% power at 5% significance was calculated to detect significant differences in patients’ health-related quality of life assessed with the SGRQ. The pre-post score achieved in the intervention group of a PR in COPD integrating family-based education and psychosocial support was used (Pre 37.9 ± 18.2 vs. Post 31.4 ± 18.7, *p* < 0.001) [27], resulting in a total sample size of 73 participants. In PR programmes, dropout rates are approximately 20 to 40% [89, 90]. Therefore, 102 participants will be recruited. Sample size calculation was performed using G*Power 3.1.3 (Universität Düsseldorf, Düsseldorf, Germany).

### Data management and statistical analysis

All variables will be processed in IBM SPSS or MS Excel software. Descriptive statistics, including frequencies, means and standard deviations, medians and interquartile ranges, will be used as appropriate. Short- and medium-term effects of the community-based PR programmes will be verified using paired t-test or Wilcoxon signed-rank tests, accordingly to data normality. Mean scores of continuous variables will be compared between patients and their caregivers using independent samples t-test or Mann Whitney U test, depending on the variable distribution. Pearson correlation coefficient [91] and Bland and Altman plots [92] for continuous variables and Cohen’s k [93] for categorical variables, will be applied to study the relationship and agreement between patients and caregivers. Relationships between variables will be explored with inferential, correlational and univariate/multivariate analyses in SPSS. Differences between the EG and CG at different time points will be assessed using a two-way ANOVA with repeated measures (continuous data), Kruskal-Wallis (ordinal data) and Chi-square or Fisher exact probability tests (nominal data). If missing data is found during the study follow up, the generalized estimating equation’ models will be applied. This method is an extension of generalized linear models to longitudinal data which permits the inclusion of time-dependent variables and the analysis of incomplete data (without imputing missing data), common in longitudinal health studies [94]. A significance level of 0.05 will be used.

Whenever possible, minimal clinically important differences (MCID) will be established, following the current recommendations to integrate both anchor-based and distribution-based approaches [95, 96]. The final MCID for each measure will be pooled using MetaXL 5.3 (EpiGear International, Queensland, Australia), with the input data being the MCID generated by each anchor- and distribution-based method and, when appropriate, the respective confidence interval. A quality effects model [97] will be used and anchor-based methods will weigh more than distribution methods (i.e., 2/3 against 1/3) [98].

A cost-benefit analysis will be conducted to determine the economic value of the perceived social value of community-based PR programmes. This analysis allows for the aggregation of both health and non-health benefits and costs of the PR programme and provides useful and quantifiable information [99, 100], not only for patients and health care institutions, but also for decision makers [101].

Focusing on the frequency and length of exacerbations, healthcare utilisation costs and quality of life gains, along with several indirect costs and benefits associated with PR implementation, including productivity loss of patients and caregivers who provide assistance, working, transportation costs, administrative costs, opportunity costs, sickness benefits payed to the patient or professional training and recruiting costs, three complementary data analysis will be held: cost:-effectiveness, −utility and -benefit.

As recent studies on COPD have demonstrated, it is suitable for cost-effectiveness analysis to rest on the ratio *incremental cost per exacerbation/healthcare utilisation avoidance* [102] aiming to compare relative costs and outcomes of PR. Then, to assess the expected impact on patients’ health-related quality of life, cost-utility analysis computes the measures of quality adjusted life years (QALY) [103] and healthy years equivalents (HYEs) [104] and determines the incremental cost per QALY/HYE gained. Finally, to account for the monetary translation of positive and negative effects of community-based PR programmes, cost-benefit analysis will be performed by determining the measures of net present monetary benefit and economic internal rate of return [105], along with a sensitivity analysis to control for the uncertainty on the assessment of costs and benefits associated to the community-based PR programmes [106, 107].

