**Methods:**

A 12-week community-based PR will be implemented in primary healthcare centres where programmes are not available. Healthcare professionals will be trained. 73 patients with CRD and their caregivers (dyads patient-caregivers) will compose the experimental group. The control group will include dyads age- and disease-matched willing to collaborate in data collection but not in PR. Patients/family-centred outcomes will be dyspnoea (modified Medical Research Council Questionnaire), fatigue (Checklist of individual strength and Functional assessment of chronic illness therapy – fatigue), cough and sputum (Leicester cough questionnaire and Cough and sputum assessment questionnaire), impact of the disease (COPD Assessment Test), emotional state (The Hospital Anxiety and Depression Scale), number of exacerbations, healthcare utilisation, health-related quality of life and family adaptability/cohesion (Family Adaptation and Cohesion Scale). Other clinical outcomes will be peripheral (biceps and quadriceps-hand held dynamometer, 1 or 10 repetition-maximum) and respiratory (maximal inspiratory and expiratory pressures) muscle strength, muscle thickness and cross sectional area (biceps brachialis, rectus femoris and diaphragm-ultrasound imaging), exercise capacity (six-minute walk test and one-minute sit to stand test), balance (brief-balance evaluation systems test) and physical activity (accelerometer). Data will be collected at baseline, at 12 weeks, at 3- and 6-months post-PR.

Changes in the outcome measures will be compared between groups, after multivariate adjustment for possible confounders, and effect sizes will be calculated. A cost-benefit analysis will be conducted.

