## Methods

### Aims

The main goal of this project is to implement an innovative community-based PR programme and assess its cost-benefit. The primary objectives are to:1.1.Investigate the short- and medium-term effects of community-based PR programmes, implemented with minimal resources and with local healthcare professionals, in patients and caregiver’s health-related quality of life;1.2.Investigate the cost-benefit of the community-based PR programmes on acute exacerbations and healthcare utilisation, to determine whether the intrinsic perceived social value of such programmes have identifiable benefits and, consequently, measurable economic value for society.

The following secondary objectives will be addressed:2.1To explore the short- and medium-term effects of community-based PR programmes on patients and caregivers’ symptoms, impact of the disease, family adaptability/cohesion, peripheral and respiratory muscle strength, exercise capacity, balance and physical activity.2.2To explore differences between patients and caregivers’ who participate and those who did not participate in community-based PR programmes in relation to dyspnoea, fatigue, cough, impact of the disease, emotional state, health-related quality of life, number of exacerbations, healthcare utilization, family adaptability/cohesion, peripheral and respiratory muscle strength and thickness, exercise capacity, balance and physical activity.2.3To explore associations between patients and caregivers’ outcomes of dyspnoea, fatigue, cough, impact of the disease, emotional state, number of exacerbations, healthcare utilisation, family adaptability/cohesion, peripheral and respiratory muscle strength and thickness, exercise capacity, balance and physical activity, pre-post community-based PR programmes.2.4To investigate the short-term effects of community-based PR programmes on patients’ peripheral muscle (quadriceps and biceps) and diaphragm thickness, cross sectional area, echointensity and motion measured resorting to ultrasound imaging.

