### Study design, setting and recruitment

A real-world non-randomised controlled study conducted in the community has been designed. Coordinators of primary healthcare centres will be approached in an arranged meeting to explain the study and those interested to participate will be asked to identify the multidisciplinary team available in their primary healthcare centre. Indication for the minimum staff required will be provided, i.e., a physician, a physiotherapist and a nurse; however, emphasis on the importance to include other professionals (e.g., nutritionist, psychologist, social worker), if available, will be given, following the international recommendations [28, 39, 40]. General practitioners and/or pulmonologists will identify eligible stable patients with a CRD (e.g., COPD, asthma, asthma-COPD overlap, interstitial lung disease, etc.) and their caregivers, and explain the study. Only patients and caregivers with interest in participating will be contacted by the researchers. A meeting will then be arranged to provide written and oral information about the study and collect the informed consent (Additional file 1). The researchers also explained that all data would be kept in databases password protected, using codes and their names would never be disclosed, ensuring the confidentiality and anonymity of all data. Two groups will be composed, experimental (EG) and control (CG). The EG will include patients and caregivers wanting to participate in a 12-week community-based PR programme and the CG will include those age- and disease-matched willing to collaborate in data collection but not in the PR programme. Recruitment started in January 2019, with final data collection expected to be completed in December 2019.

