### Data collection

Sociodemographic (age, sex, educational level, marital and working status), anthropometric (height and weight to calculate the body mass index) and general clinical data (long-term oxygen, non-invasive ventilation, medical history, comorbidities to calculate the Charlson Comorbidity Index [45] and medication) will first be collected with a structured questionnaire to characterise the sample and will be followed by a lung function test with spirometry [46].

The primary outcome measure will be health-related quality of life, assessed with the St. George Respiratory Questionnaire (SGRQ) [47] in patients and with the World Health Organization Quality of Life Bref Questionnaire [48, 49] in caregivers. The number of acute exacerbations, healthcare utilisation costs and collateral costs (e.g. transport costs, work absence costs, sickness benefits) will also be collected to conduct the cost-benefit analysis [50].

In addition, the following secondary outcomes will be assessed: symptoms of dyspnoea (modified Medical Research Council Questionnaire [mMRC]) [51], fatigue (Checklist of individual strength [CIS-20]) [52] and Functional assessment of chronic illness therapy – fatigue [FACIT-F]) [53, 54], cough and sputum (Leicester cough questionnaire [LCQ] [55] and Cough and sputum assessment questionnaire [CASA-Q]) [56], impact of the disease (COPD Assessment Test [CAT]) [57, 58], emotional status (The Hospital Anxiety and Depression Scale [HADS]) [59, 60], Family Adaptation and Cohesion Scales [FACES-IV]) [61, 62], peripheral (biceps and quadriceps with the hand held dynamometer, 1 [1-RM] or 10 [10-RM] repetition-maximum) [63, 64] and inspiratory and expiratory muscle strength (respiratory pressure meter) [65], exercise capacity (six-minute walk test [6MWT] and one-minute sit to stand test [1-min STS]) [66, 67], balance (brief-balance evaluation systems test [Brief-BESTest]) [68] and physical activity (accelerometer) [14]. Peripheral muscle (rectus femoris and biceps brachialli) and diaphragm thickness, cross sectional area [69, 70] and echointensity [71], excursion and M-Mode Index of Obstruction (MIO) [72–74], will be measured with ultrasound images – ImageJ and Matlab software. Global rating of change scale [75] for fatigue, cough, sputum, peripheral and respiratory muscle strength and balance will also be collected.

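### The primary quality-of-life objective is tied to within-group paired tests, while the planned comparison with controls is left to an exploratory objective and without the adjustment the abstract promises

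*Protocol article*

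**What the plan says.** All references are to the protocol article.

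- **Aims, objective 1.1 (primary):** "Investigate the short- and medium-term effects of community-based PR programmes, implemented with minimal resources and with local healthcare professionals", on the health-related quality of life of patients and caregivers. No comparator is named.
- **Aims, objective 2.2 (secondary):** the comparison of participants with "those who did not participate in community-based PR programmes". It is framed as exploration, and its outcome list includes health-related quality of life.
- **Data collection:** the primary outcome is the SGRQ in patients and the WHOQOL-BREF in caregivers.
- **Data management and statistical analysis:** "Short- and medium-term effects of the community-based PR programmes will be verified using paired t-test or Wilcoxon signed-rank tests", depending on normality. A later, separate sentence reads: "Differences between the EG and CG at different time points will be assessed using a two-way ANOVA with repeated measures (continuous data"). Generalised estimating equations (GEE) replace this if follow-up data are missing. Neither sentence refers to an objective by number, and the between-group sentence names no covariates.
- **Abstract, Methods:** "Changes in the outcome measures will be compared between groups, after multivariate adjustment for possible confounders".
- **Sample size:** 80% power at 5% significance, from the pre-post SGRQ scores of a treated group (37.9 ± 18.2 to 31.4 ± 18.7). This gives 73 participants in total, with 102 to be recruited. The abstract instead places 73 patients in the EG.
- **Study design, setting and recruitment:** controls are matched on age and disease and are people who do not want PR. "Recruitment started in January 2019, with final data collection expected to be completed in December 2019".

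**The concern.** A significant paired test shows that scores moved. It does not show that PR moved them. Regression to the mean, general time trends, changes in usual care and season all enter the within-group change point for point. The study measures matched controls at the same visits, which is the information needed to remove change common to both groups. Yet the wording that defines the primary question leads to a test that does not use them.

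At stake is the causal reading of the main quality-of-life result. Followed as written, the plan lets the study report that PR effects were verified when the two groups may have changed by similar amounts. If scores tend to worsen over time, it could equally miss a real benefit.

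**Working it through.** **1. Which analysis answers objective 1.1?** Three features point to the paired test:
- The analysis section attaches the wording of objective 1.1 (short- and medium-term effects of the programmes) to paired tests.
- The EG-CG contrast matches objective 2.2, which is secondary and exploratory.
- The sample size uses a pre-post change in one treated group, with no between-group difference and no allocation ratio.

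This is an inference from wording and structure, since no analysis is labelled primary.

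**2. The plan's own figure.** The mean change is 37.9 − 31.4 = 6.5. The SD of change is √(18.2² + 18.7² − 2·r·18.2·18.7), where r is the pre-post correlation, which is not given. Exact paired t-test, two-sided 5%, 80% power:

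| r | SD of change | n |
|---|---|---|
| 0.30 | 21.83 | 91 |
| 0.44 | 19.53 | 73 |
| 0.50 | 18.46 | 66 |
| 0.70 | 14.30 | 40 |
| 0.80 | 11.68 | 28 |

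So 73 fits a two-sided paired test at r of about 0.44. A one-sided test at r = 0.3 gives 72. The article states neither r nor sidedness, so 73 is neither confirmed nor refuted. Below, r = 0.44 (SD about 19.5) is a back-solved assumption.

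**3. Effect of drift on the paired test.** Assume no PR effect and a drift of c points from other causes. The article gives no value for c. The noncentrality is c·√n / SD:
- n = 73, c = 2: 2 × 8.544 / 19.53 = 0.87, so the test is significant in 14% of studies.
- n = 73, c = 3: 1.31, so 25%.
- n = 36 (half of 73 in the EG), c = 2: 0.61, so 9%.
- n = 36, c = 3: 0.92, so 15%.

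The nominal rate is 5%. With n = 73 and r from 0.44 to 0.8, the ranges are 14-30% for c = 2 and 25-58% for c = 3. The test is two-sided, so these probabilities are the same for worsening. In that case, drift would also offset a true benefit.

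**4. Calendar, as one example of a time effect.** Twelve weeks (84 days) plus 6 months (about 183 days) is 267 days. If every participant completes follow-up by 31 December 2019, the last baseline is about 8 April 2019. Baselines then fall between January and early April, and 12-week visits between about late March and early July. Time since baseline and season would be nearly aligned.

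**5. Power of the between-group contrast.** Assume a true difference of 6.5 (that is, no CG change), 1:1 groups, two-sided 5% and r = 0.44. The SD is 19.53 for change scores, or 18.7 × √(1 − 0.44²) = 16.79 after baseline adjustment.

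| Evaluable patients | Change score | Baseline-adjusted |
|---|---|---|
| 36 + 37 (73 in total) | 29% | 37% |
| 73 + 73 | 51% | 64% |

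For 80% power, about 143 per group (change score) or 105 per group (baseline-adjusted) are needed. A higher r eases this: at r = 0.7, the change-score comparison needs 77 per group.

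**The case against.** The strongest reply is that the comparison already exists. The analysis section plans an EG-CG repeated-measures ANOVA, with GEE for incomplete data, and objective 2.2 covers health-related quality of life. A reader might infer that the control group is ignored. The documents do not support that: the defect is which analysis answers the primary objective. Nor does the abstract say the opposite of the methods, since both contain a between-group comparison. The mismatch is the confounder adjustment, which appears in the abstract but not in the between-group sentence.

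The link from objective 1.1 to the paired test is also inferred. Secondary objective 2.1 uses the same wording, and the ultrasound measures are taken in the EG only, so a within-group test is the only option there. This is fair. But the same sentence is the only one that matches objective 1.1, and the pre-post sample size fits it.

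A reader might extend the point to exacerbations and healthcare utilisation. The article sends those to an economic analysis with incremental ratios, which implies a comparator, so the extension does not hold. Season is not mentioned in the article. Its size and direction are unknown, and the dates rest on an expected completion.

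Finally, controls are people who declined PR, so a between-group estimate carries self-selection bias. That stands. It argues for adjustment and cautious wording, and it does not make the uncontrolled change a better answer.

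**Conclusion.** The concern holds in this form: by matching wording and by the basis of the sample size, objective 1.1 is answered by within-group tests that cannot isolate a PR effect. The planned EG-CG contrast is left to an exploratory objective, without the adjustment promised in the abstract.

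The size of the resulting error cannot be known from the article. The false-positive rates above are illustrations that depend on an assumed drift, an assumed correlation and an EG size that the article gives inconsistently. What does not depend on those assumptions is that any change unrelated to PR passes in full into the paired estimate, in either direction. This should be corrected before the primary result is interpreted.

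**What to change.** - State in the analysis section that objective 1.1 is answered by the EG-minus-CG difference in SGRQ change from baseline to 12 weeks, with the same contrast for WHOQOL-BREF in caregivers. Adjust for baseline score and for named confounders already collected (for example age, sex, Charlson index, lung function). Treat 3 and 6 months post-PR as supportive.
- Keep the paired tests as description of within-group change, without causal wording.
- Reconcile the abstract, the Aims and the analysis section on which comparison leads and on adjustment.
- Restate the sample size or the power for this contrast, giving the assumed correlation, sidedness and group sizes. Settle whether 73 is the EG or the total.

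**Cost.** No new variables or visits are needed, but this is more than a wording change. The 80% power claim is lost at the stated numbers, and recovering it would probably need more patients, while the article already expects difficulty recruiting controls. If the numbers cannot grow, report the lower power openly and rely on the estimate with its confidence interval. Residual self-selection should be listed as a limitation, and causal wording should stay cautious for the between-group result too.

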### Eligibility criteria

Patients will be eligible if they are diagnosed with a CRD [43, 44] and clinically stable in the previous month (i.e., no hospital admissions, exacerbations or changes in medication for the cardiorespiratory system). Exclusion criteria will be the presence of any clinical condition that can preclude participants of being involved in the community-based PR programme, such as, signs of cognitive impairment (e.g. dementia) or presence of a significant cardiovascular (e.g. symptomatic ischaemic cardiac disease), neurological (e.g. neuromuscular dystrophy disease) or musculoskeletal disease (e.g. important kyphoscoliosis). Caregivers will be included if they are: ≥18 years old and living with or providing physical/supportive care to the patient, and excluded if they are unable to cooperate.

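### Patients and their own caregivers form linked pairs, but their means are to be compared with tests for independent samples

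*Protocol article*

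**What the plan says.** The Abstract (Methods) sets the unit of recruitment: "73 patients with CRD and their caregivers (dyads patient-caregivers) will compose the experimental group". The control group is also made up of dyads. Under Eligibility criteria, a caregiver qualifies by "living with or providing physical/supportive care to the patient", so each caregiver is tied to a particular patient.

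The section on data management and statistical analysis then makes four separate provisions:

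- Programme effects over time "will be verified using paired t-test or Wilcoxon signed-rank tests".
- Continuous scores are "compared between patients and their caregivers using independent samples t-test or Mann Whitney U test".
- Pearson correlation, Bland-Altman plots and Cohen's k are used "to study the relationship and agreement between patients and caregivers".
- "Differences between the EG and CG at different time points will be assessed using a two-way ANOVA with repeated measures", with other tests for ordinal and nominal data.

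Generalised estimating equations are named as a fallback if follow-up data are missing. On significance the section says only: "A significance level of 0.05 will be used".

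**The concern.** The independent-samples t-test and the Mann-Whitney U test both take the two samples to be unrelated. Here every caregiver is linked to one patient by living with or caring for that person, and their scores on a shared scale may well be correlated. The tests leave out the within-dyad covariance, so the standard error of the mean difference is wrong. If the correlation is positive, the test is conservative and loses power. If it is negative, the test rejects too often.

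The plan also conflicts with itself. The centre line of a Bland-Altman plot is the mean within-dyad difference, the same quantity that the t-test examines. The two adjacent analyses would therefore attach different precision to one estimate. The plan cannot take the correlation to be zero either, since it sets out to study the relationship between the two members, and objective 2.3 asks about associations between their outcomes.

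**Working it through.** **Which comparison the sentence governs.** Experimental versus control has its own sentence and methods, and change over time has paired tests. The quoted sentence can therefore only mean patients against their own caregivers. The estimating-equation fallback is triggered by missing follow-up data and does not mention clustering by dyad, so it does not correct the problem.

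**The plan's own figure.** None is given for this comparison. The 73 under Sample size was derived for the pre-post change in patients' SGRQ, and nothing below depends on how it was obtained.

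**Inputs.**

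- From the protocol article: significance level 0.05 (taken as two-sided, since this is not stated); dyad structure; 73 dyads in the experimental group (Abstract).
- Assumed: equal SD σ in patients and caregivers; within-dyad correlation ρ of 0.2, 0.3 or 0.5, with -0.2 to show the other direction; all 73 dyads complete; a true difference of 0.35 SD for power.

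**Standard error.** With n dyads:

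- as planned: σ√(2/n) = σ√(2/73) = 0.166σ
- allowing for pairing: σ√(2(1−ρ)/n); at ρ = 0.3 this is σ√(1.4/73) = 0.138σ
- ratio: 1/√(1−ρ); at ρ = 0.3 this is 1/√0.7 = 1.195

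**True type I error.** In large samples it is 2[1 − Φ(1.96/√(1−ρ))]. At ρ = 0.3, 1.96/√0.7 = 2.343, which gives 0.019.

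Neither the ratio nor the large-sample type I error depends on n.

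**Simulation check.** The formulas were checked with 40,000 simulated data sets of 73 dyads (3,000 for Mann-Whitney):

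| ρ | SE ratio | Type I error, formula | Unpaired t, simulated | Mann-Whitney, simulated | Paired t, simulated |
|---|---|---|---|---|---|
| -0.2 | 0.913 | 0.074 | 0.073 | 0.072 | 0.051 |
| 0 | 1.000 | 0.050 | 0.050 | 0.049 | 0.049 |
| 0.2 | 1.118 | 0.028 | 0.029 | 0.029 | 0.050 |
| 0.3 | 1.195 | 0.019 | 0.018 | 0.023 | 0.048 |
| 0.5 | 1.414 | 0.006 | 0.006 | 0.007 | 0.048 |

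The planned tests hold 5% only at ρ = 0. The paired t-test holds it throughout.

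**Power for a 0.35 SD difference, 73 dyads, from the same simulations.**

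| ρ | Unpaired t | Paired t |
|---|---|---|
| 0.2 | 0.558 | 0.641 |
| 0.3 | 0.563 | 0.705 |
| 0.5 | 0.578 | 0.838 |

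**The case against.** The strongest reply is that little hangs on this comparison. No objective under Aims asks for a mean difference between patients and caregivers: objective 2.2 compares participants with non-participants, and objective 2.3 asks for associations, which the correlation and agreement methods address. The comparison cannot involve the primary outcome, because patients complete the SGRQ and caregivers the WHO quality-of-life questionnaire. The main pre-post tests are already paired, and the 73 and 102 do not change. For people who live together or care for one another, positive correlation is the likelier direction. The usual consequence is then p-values that are too large, not false positives. The 7.4% figure needs a negative correlation, for which the documents give no support.

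All of that stands, and it limits the importance of the point. It is also fair that 73 complete dyads and 0.35 SD are illustrative: the article expects difficulty in recruiting caregivers and 20 to 40% dropout, so the number of complete dyads is unknown. That affects the power figures but not the standard-error ratio.

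What does not stand is any reading that makes the named tests suitable. Nor is this a detail left to a fuller document: the article names specific tests, and their central assumption conflicts with its own design.

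**Conclusion.** The concern holds. The named tests do not fit dyadic data and are inconsistent with the agreement methods beside them. Under the assumed correlations of 0.2 to 0.5 with equal variances, the standard error is overstated by 12% to 41% and the true type I error falls to between 2.8% and 0.6%. At correlation 0.3, power for the illustrative difference drops from about 70% to about 56%. The likely harm is missed differences between patients and caregivers; inflated false positives would need a negative correlation. The error is confined to a secondary comparison, so it should be corrected but does not threaten the primary results.

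**What to change.** Replace the independent-samples tests in that sentence with a paired t-test, or a Wilcoxon signed-rank test, on within-dyad differences. State that the comparison covers only scales completed by both members.

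Paired tests drop any dyad with one member missing. Since the article anticipates difficulty in recruiting caregivers, a better choice may be a mixed model with a dyad random effect and terms for role (patient or caregiver), time and their interaction; estimating equations clustered on dyad are an alternative. Either uses incomplete dyads and suits the repeated visits, provided that the dependence between one person's visits is modelled as well.

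The cost is one sentence and the choice between these options. Data collection, recruitment and the sample size are unchanged.
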